### Sample size

The trial is powered to detect an independent effect of the two interventions on observed SDM, as assessed with the OPTION12 [62, 63], a widely used instrument to assess SDM in consultations. There is no agreement on what constitutes a clinically meaningful difference on the OPTION12. The sizes of the effects of SDM interventions on OPTION12, including decision aids and physician training across different specialties and in both simulated and clinical settings, range from 0.5 to 1.5 [41, 64, 65]. As most reported large effect sizes, we adopted an effect size of d = 0.8 in the sample size calculation. We expected that the effect of the combination of the oncologist training and the patient communication aid will be larger, but not twice as large (estimated effect size = 1.2). To account for this hypothesized antagonistic interaction [66], we decided to adopt a parallel group design instead of a factorial design. Hence, we will examine the effect of the oncologist training among patients allocated to the control condition (between-oncologist comparison) and the effect of the patient communication aid among untrained oncologists (within-oncologist comparison).

SDM will vary by oncologist. ICC’s for the OPTION12 reported in literature [67, 68] and personal communication ([name], Leiden University, the Netherland, May 2014; [name], University Medical Center Hamburg, Germany, July 2014) range from 0.11 to 0.60. In a sample of 47 audio-recorded consultations meeting the same eligibility criteria as the current trial [20], an ICC of 0.19 for OPTION12 scores was demonstrated (unpublished). Since the ICC was 0.20 or lower in the majority of these data sets, a value of 0.20 was adopted in the sample size calculation.

Sample size calculation was based on the effect of the oncologist training (between-oncologist comparison; two-sided t-test taking into account clustered data). The above mentioned criteria, along with a power of >80% and α of 0.05, resulted in a required sample size of 24 oncologists and 192 patients (12 oncologists per arm and 8 patients per oncologist; power = 0.84).

### Recruitment

#### Oncologists

To include 24 oncologists (in training), the medical oncology departments of both academic and non-academic hospitals are approached through existing networks until at least 30 eligible and consenting oncologists are recruited (considering potential drop-out of 25%). Oncologists are informed about the study by both the local investigator and the principal investigator; are provided with an information letter and are asked for written informed consent.

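### A recruitment floor of 30 oncologists covers 20% drop-out, not the stated 25%; at 25% the floor leaves 22 or 23 of the required 24, a minor correction

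*Protocol article*

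**What the plan says.** The Sample size section of the protocol article bases the calculation on the training effect, described as a "between-oncologist comparison; two-sided t-test taking into account clustered data". Its inputs are a standardised effect ("we adopted an effect size of d = 0.8 in the sample size calculation"), an intraclass correlation ("a value of 0.20 was adopted in the sample size calculation") and error rates ("along with a power of >80% and α of 0.05"). The result is "24 oncologists and 192 patients (12 oncologists per arm and 8 patients per oncologist; power = 0.84".

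The oncologist part of the Recruitment section opens with the purpose, "To include 24 oncologists (in training"), and then says that departments are approached "until at least 30 eligible and consenting oncologists are recruited (considering potential drop-out of 25" per cent). It gives no base for the percentage other than the oncologists recruited.

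The patient part, which follows directly, assumes a 66% response rate and concludes that 291 patients must be approached to include 192.

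**The concern.** One sentence gives a target (24), a recruitment floor (30) and a drop-out allowance (25%), and any two of them contradict the third. Drop-out acts on those recruited, so the number recruited should be the target divided by the proportion retained.

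The oncologist is the randomised cluster in the comparison on which the trial was sized, so losing oncologists costs more power than losing the same fraction of patients evenly across oncologists. A reader of the sentence would believe that a quarter of the oncologists could be lost with 24 oncologists and a power of 0.84 intact. By the protocol's own figures that is not so. What remains to be settled is how much power is lost, and whether it falls below the level the protocol set itself.

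**Working it through.** **Inputs from the protocol article.** Required oncologists 24 (12 per arm), 8 patients each, d = 0.8, ICC = 0.20, two-sided α = 0.05, power above 80% (Sample size). Floor of 30 and drop-out of 25% (Recruitment, Oncologists). Response rate 66% (Recruitment, Patients).

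**Assumption.** The training effect is estimated among control-condition patients only. I take m = 4 of the 8 patients per oncologist, that is, an even split within each oncologist.

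**1. The recruitment figure.**
- 24 × (1 + 0.25) = 30, which is the stated floor.
- 24/(1 − 0.25) = 32, which is what 25% drop-out requires.
- 30 × 0.75 = 22.5, so 22 or 23 remain, 1 or 2 short of 24.
- 1 − 24/30 = 0.20, the drop-out that 30 recruits do cover.
- For comparison, the patient figure divides: 192/0.66 = 290.9, stated as 291. The two adjacent subsections are therefore inflated differently.

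**2. The stated power.** For k₁ and k₂ oncologists per arm, the design effect is 1 + (m − 1) × ICC = 1 + 3 × 0.20 = 1.6. The standard error of the standardised difference is √[1.6/(4k₁) + 1.6/(4k₂)], the noncentrality is 0.8/SE, and power comes from the noncentral t distribution with k₁ + k₂ − 2 degrees of freedom.

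At 12 + 12: SE = √(2 × 1.6/48) = 0.2582, noncentrality = 0.8/0.2582 = 3.098, 22 df, power 0.8415. This reproduces the stated 0.84, so the method and the assumption of 4 control patients fit the protocol's own calculation.

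**3. Power after the stated loss.**

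| Oncologists per arm | Total | SE | Noncentrality | df | Power |
|---|---|---|---|---|---|
| 12 + 12 | 24 | 0.2582 | 3.098 | 22 | 0.8415 |
| 11 + 12 | 23 | 0.2640 | 3.030 | 21 | 0.8236 |
| 11 + 11 | 22 | 0.2697 | 2.967 | 20 | 0.8055 |
| 10 + 12 | 22 | 0.2708 | 2.954 | 20 | 0.8023 |
| 9 + 13 | 22 | 0.2743 | 2.917 | 20 | 0.7924 |
| 10 + 11 | 21 | 0.2763 | 2.895 | 19 | 0.7841 |

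The loss against 0.8415 is about 0.02 with 23 oncologists and about 0.04 with 22. Power falls below 0.80 only with a clearly uneven loss (9 + 13) or one further oncologist lost (10 + 11).

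**4. Patients.** At 8 per oncologist, 22 × 8 = 176 and 23 × 8 = 184, against 192. If 192 patients were still recruited over the remaining oncologists (192/22 = 8.7 or 192/23 = 8.3 each, half of them controls), power would be about 0.82 with 11 + 11 and 0.83 with 11 + 12.

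**The case against.** The strongest reply concerns weight, and most of it stands.

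- **The design criterion is power above 80%.** The 0.84 is what 12 per arm happens to give. At 22 or 23 completers in near-balanced arms the criterion is still met. This stands, and it is why the point is minor.
- **The 30 is a floor and the 25% a potential loss.** The text permits more recruits, and the allowance need not be used up. This also stands: the protocol does not fix a shortfall. But a floor is where recruitment may stop, and stopping there does not provide for the loss that the same sentence names.
- **The patient shortfall is conditional.** Eight recordings per oncologist is an aim, and the target of 192 is set separately. The text does not say when drop-out occurs. Under the stated intention-to-treat rule, eligible consultations recorded before an oncologist leaves would be analysed. So 176 to 184 holds only at 8 each, with nothing contributed by those who leave.
- **The 25% might mean a quarter of 24, that is, six extra.** This does not rescue the sentence. It is the same calculation as 24 × 1.25, and the sentence names no base other than the oncologists recruited.

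A reader might go further and infer that the trial is underpowered for its primary comparison, or that the patient target must be missed. The documents support neither. Nor do they prove how the 30 was obtained: multiplication by 1.25 gives it exactly, but no formula is printed.

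**Conclusion.** The sentence is wrong as written: 30 recruited oncologists do not provide 24 after 25% drop-out. That part needs no assumption and does not depend on how the 30 was reached. The floor is two oncologists below the number that matches the stated rate.

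The consequence is small. If recruitment stops at 30 and the whole 25% is lost, power for the training effect is about 0.81 to 0.82 instead of 0.84. This rests on d = 0.8, ICC 0.20, 4 control patients per oncologist and near-balanced arms. The margin over 80% is thin, but it is there. This is a minor correction to a planning figure; the design and the primary comparison stand.

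**What to change.** Correct the oncologist recruitment sentence in one of two ways:

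1. Keep the floor of 30 and state that it allows for 20% drop-out.
2. Keep 25% and state that 22 or 23 oncologists are then expected to complete, with power of about 0.81 to 0.82 under the protocol's own inputs and 4 control patients each.

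If further oncologists are available, a floor of 32 makes the sentence correct with 25% and 24 both unchanged.

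Either rewording costs one sentence and a slightly less favourable drop-out allowance or power figure. Raising the floor costs the recruitment of two more oncologists, and the training of about one of them. No part of the analysis changes.

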#### Patients

In a previous observational study on doctor-patient communication, the response rate was 78%. We more conservatively estimated the response rate to be 66% for this RCT, implying that *n* = 291 patients need to be approached to include *n* = 192 patients. Roles and procedures for inclusion differ per center. Eligible patients are identified from the outpatient clinic agendas at least one week in advance by the oncologist (in the coordinating hospital supported by the research team), or by a designated oncologist or nurse. Depending by center, either the treating oncologist, a nurse or trial officer contacts the patient by telephone, explains the study in general terms and asks for permission to provide the patient’s contact details (along with gender, tumor type, treating oncologist, date of consultation and type of consultation) to the coordinating research team. The coordinating research team then informs the patient by telephone about the study in more detail. Patients are told that the aim of the study is to investigate the effect of an oncologist training and a patient communication aid on doctor-patient communication about treatment. Since time between initial contact and consultation is often short, patients will be randomized immediately after providing oral informed consent. Patients will subsequently receive a written information letter with information about the study and a written informed consent form. This package will include information about the condition they were assigned to (and, depending on condition, the communication aid). Patients are requested to bring the consent forms to the consultation, where they will sign the forms together with either the oncologist or a research associate. Patients will be given the opportunity to ask questions. Companions are also asked to provided written consent for audio-recording the consultation. It is stressed that patients can withdraw consent at any time. In all stages, reasons to decline participation or drop out will be documented.

### Procedure and time line

Figure 1 shows the time line for oncologists and patients. *Oncologists* will participate in a simulated encounter with an actor patient (standardized patient assessment) at two points in time, with 2–3 months in between. After each assessment they will complete a questionnaire (T0 and T1). Oncologists randomized to the training condition will receive the skills training between the first and second standardized patient assessment. Subsequently, for each oncologist, we aim to audio-record consultations with 8 patients in daily clinical practice with a small audio-recording device. Either a research associate or the oncologist will operate the recorder. The research associate will not attend the consultation. After each consultation, oncologists complete a short questionnaire (T2).

**Fig. 1 Fig1:**
[figure not shown]
Assessments for oncologists and patients

Patients will receive a baseline questionnaire (T0) by postal mail at inclusion. They will be asked to bring the completed questionnaire to the consultation. Before the consultation, patients will be asked to complete a one page questionnaire (T1). All subsequent questionnaires (i.e., T2 at one week, T3 at 3 months and T4 at 6 months post-consultation) will be sent by postal mail, including return envelopes. Reminders are sent once, if a questionnaire has not been returned within 2 weeks. Clinical data will be collected from patients’ medical files by a research associate or nurse.

### Randomization

#### Oncologists (in training)

Oncologists are randomized to receive training or continue their standard practice. Randomization stratifies for working experience (staff versus oncologist in training). Randomization occurs in blocks of 2. To prevent predictable allocation, oncologists are allocated in sets of at least two ‘of a kind’ (either staff or in training). Randomization occurs per hospital to make sure that in each hospital approximately half of the participating oncologists is trained. Randomization lists are created by an independent methodologist. Randomization is performed by an independent researcher.

#### Patients

Patients are randomized to receive the communication aid or ‘usual care’. Randomization is performed in ALEA software for randomization in clinical trials. Randomization stratifies for three factors: (1) the condition of the treating oncologist (trained/untrained) and (2) working experience of the treating oncologist (staff/in training) and (3) the type of consultation (initial treatment planning consultation/evaluative consultation), to ensure an equal ratio in all study arms. Stratification occurs through minimization. Stratification factor 1 (trained or untrained oncologist) receives a weight of 3; factors 2 and 3 a weight of 1. A biased coin of 5 starts to work in case of a contrast of >3 between the two conditions. Randomization data in ALEA are adjusted in three specific scenarios: (1) to change the status and experience of the treating oncologist in case patients switch oncologists after randomization, (2) exclusion of a randomized patient in case the patient does not provide final written informed consent (see Procedure) and (3) exclusion of a randomized patient if only during the consultation it turns out the patient does not meet the eligibility criteria (see Participants). These adjustments will be performed and documented by an independent methodologist.

### Blinding

*Oncologists* are not blinded for their own condition. Although they are blinded for their patients’ condition, the communication aid may come up in the consultation. They will be asked whether they know or suspect the patient to have received the aid in the questionnaire (T2) right after the consultation. *Patients* are obviously not blinded for whether they received the aid or not. They are blinded for their oncologist’s condition though. *Outcomes assessors* are blinded for the condition of the oncologist. The assessors will not be informed about the patients’ condition either, yet the aid may come up in the consultation.

### Interventions

#### Oncologist training

The training is based on a recent model of SDM [6] which integrates earlier models and distinguishes four essential steps within a SDM consultation: (1) set the SDM agenda, (2) inform about the options, (3) explore patients’ values and support preference construction, (4) make or defer a decision in agreement. The training aims to address knowledge (i.e., of definition, rationale, effect and steps of SDM), attitude (i.e., awareness of preference-sensitive decisions and personal barriers as well as motivation) and skills (i.e., ability to apply the four steps in a consultation using high quality communication skills). The training is provided in small groups (3–6 participants) by an experienced trainer (i.e., a medical psychologist with ample experience in skills training for health professionals) in two sessions of both 3.5 h. Staff members and oncologists in training are trained separately to allow for a safe training environment and a match in experience and skill level. The training adopts techniques known from behavior change theories [69], such as instruction (in a reader and face-to-face), modelling (tailor made video’s illustrating SDM with a patient with advanced cancer) and exercise (role play with professional actors). Moreover, the training explicitly addresses the transfer from skills in a simulated setting to a clinical setting. In a booster session of 1–1.5 h 6 weeks post-training, participants receive individual face-to-face feedback on a videotaped consultation with a real patient. Moreover, all participants receive a consultation room tool: a pocket-size card presenting the four SDM steps with example phrases to serve as a reminder and to support participants in taking the learned skills into practice. The training was piloted with 5 oncologists in training from two hospitals and was well evaluated, with a mean satisfaction score of 8 on a scale of 10. The training was accredited by the Netherlands Association of Internal Medicine (12 CME credits).

#### Patient communication aid

The patient communication aid is a brochure with three sections: (1) patient education about SDM, (2) Question Prompt Lists and (3) a Value Clarification Exercise. The brochure first explains that, in case of metastatic or inoperable cancer, treatment decisions depend on patient preferences. A rough distinction between two options is presented, i.e. the choice between best supportive care alone or best supportive care complemented with disease-targeted treatment, such as chemotherapy. It is mentioned that for some patients there are additional options, such as experimental treatment or postponing the start of disease-targeted treatment. In the second section, patients are presented with example questions they may wish to pose in the consultation with the oncologist. These questions are designed to allow patients to receive the information required to make an informed choice. It includes questions about topics patients may find difficult to ask, such as questions about life expectancy or foregoing disease-targeted treatment. The questions are ordered on two levels: (1) the decisional situation (i.e., *start* of new treatment or *evaluation* of current treatment) and (2) for each of these situations the available options (*start*: best supportive care, disease-targeted treatment, experimental treatment, postponing; *evaluation*: continuing treatment, dose reduction, stop/change treatment). The third section consists of a Value Clarification Exercise. Patients are invited to reflect on their values by three open-ended questions about what they find important for the upcoming period and what treatment outcomes they would or would not appreciate. These questions are supported by example answers and by four diverse narratives of simulated patients. Lastly, patients are invited to complete four scaling items forcing a choice between values (e.g., take every change on a longer life versus accepting the possibility of only a short time left). It is stressed that these questions are meant to help patients elaborate on their values and preferences. A decision is made together with the oncologist.

The tool was developed in three phases. The first version was developed based on examples from the literature [40, 51, 70, 71] as well as the consultation of experts from multiple disciplines (e.g., general practice, oncology, psychology, nursing, spiritual care and hospice care). This version was presented to patients (*n* = 13), their companions (*n* = 8) and bereaved relatives (*n* = 14) in semi-structured (focus group) interviews. Based on respondents’ feedback, a second version was created, which was piloted among 18 patients in two hospitals. Patients were asked to use the aid and were surveyed and interviewed about their evaluation. On the basis of their feedback, the final aid was designed.

### Outcomes

#### Primary outcome

The primary outcome is the level of SDM as observed in the audio-recorded consultations in clinical practice, assessed with two instruments. One is the widely used Observing Patient Involvement (OPTION) tool [41, 62, 63], a 12-item coding system of physician communicative behavior associated with SDM (see Additional File 1). Items are rated by observers on a 0–4 scale and scores are transformed to give a total out of 100. Next to the general manual, a study-specific manual will be developed. Besides the OPTION12, SDM will be assessed with the 4SDM (see Additional File 1), an instrument that is newly developed and based on the 4-stage SDM model [6]. In contrast to other SDM instruments, the 4SDM (1) only assesses essential elements of SDM, leaving out all non-specific communication skills, (2) assesses SDM, irrespective of who shows the behavior, thereby giving credit to both clinicians’ and patients’ initiatives, and (3) allows for the distinction between the four SDM steps. The 4SDM has eight items (two for each step) which are coded on a 4 point scale (0–3). The 4SDM has a general as well as a study-specific manual. In an unpublished pilot study the correlation between OPTION12 and an early version of the 4SDM was high (Spearman *r* = 0.92, *n* = 50).

Two raters blinded for the condition of the oncologists and patients, will code the consultations with the OPTION12 and the 4SDM. Consultations will be double coded; each consultation will be rated on the OPTION12 by one coder and on the 4SDM by a second coder. Before the start of coding, the two raters will be trained and calibrated. Interrater agreement (IRR) will be monitored during this process. Raters will first read the general and study specific manuals and discuss their questions with the PI. Then, the raters will independently code 2 × 3 encounters that were audio-recorded in a previous observational study in the same setting [20], using all instruments. Scores will be compared and inconsistencies will be discussed to arrive at a common interpretation of the items of both instruments. The raters will be assisted in these discussions by the principle investigator (PI). Then they will double code 10 consultations from the previous observational study: 5 consultations with the OPTION12 and 5 consultations with the 4SDM. For each set of 5, IRR will be calculated. IRR will be considered sufficient if the ICC’s and the average weighted kappa’s across items are higher than .60 (substantial agreement) [72], and the raters do not differ more than one point in their scores across items and consultations. As the number of coded consultations is low and distribution of categories skewed, many row and column totals in the matrices will contain zeros. In these cases, and in these cases only, kappa’s will be prevalence-adjusted by balancing the matrix [73]. When IRR is insufficient, scores of problematic items will be discussed. This process will be repeated until sufficient IRR is achieved. Then, raters will start coding the data collected in the CHOICE trial independently. They will alternate both instruments (5 with OPTION12, then 5 with 4SDM, then 5 with OPTION12, etc). Consultations will be randomly assigned.

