### Statistical methods

#### Primary outcome

To account for the hierarchical nature of the data, i.e. patients nested within oncologists, multilevel regression analysis will be used to test the effect of the single interventions on the observed level of SDM in the audio-recorded consultation. Analysis will be conducted separately for the OPTION12 and the 4SDM. Random intercept and slope models will be examined. The effect of the oncologist training (level of oncologists) will be established among patients who did not receive a communication aid. The effect of the communication aid (level of patients) will be established among patients of untrained oncologists. Effects with two-sided *p*-values < .05 will be considered significant; 95CI’s as well as effect sizes will be provided. As the OPTION12 is currently the most widely used instrument to assess SDM, an intervention will be considered effective if it had a significant effect on OPTION12 scores. Baseline differences across arms on background characteristics (patient age, gender, educational level) as well as patients’ baseline measures will be examined with the appropriate statistical tests (ANOVA, Chi-squared tests). All analyses of effectiveness will be controlled for differences between arms at baseline as well as the two stratification variables (working status oncologist, type of consultation). All analyses will be intention-to-treat, i.e., all eligible consultations will be included in the analysis (irrespective of whether the communication aid was actually received or read; or whether the oncologist received the full training package).

The hypothesized additional effect of the combined intervention will most likely be smaller than the effects of the single interventions (RQ1). That is, combining the two is hypothesized to increase but not to double the effect of the single interventions. The combination of the training and the aid will be considered more effective than either or both single interventions if (1) the effect size of the combination compared to care as usual is statistically significant and (2) is at least 150% of the effect size of either or both single interventions. The study is not powered to statistically test the difference between the combination and the single interventions.

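### Rater is missing from the stated adjustment set although each primary score comes from one of two raters: a small, avoidable loss of precision, not a threat to validity

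*Protocol article*

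**What the plan says.** Protocol article, Outcomes, Primary outcome: two raters code the audio-recordings, and "each consultation will be rated on the OPTION12 by one coder and on the 4SDM by a second coder". The article calls this double coding, but no trial consultation is scored twice on the same SDM instrument. The raters switch instruments after every five recordings, so each supplies about half of the OPTION12 scores. On allocation to raters the text says "Consultations will be randomly assigned".

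Before coding starts, the raters are calibrated on recordings from an earlier study, with "5 consultations with the OPTION12 and 5 consultations with the 4SDM" coded by both. Agreement suffices when the ICCs and the average weighted kappas exceed .60 and the "raters do not differ more than one point in their scores across items and consultations". After that, the "raters will start coding the data collected in the CHOICE trial independently".

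Protocol article, Statistical methods, Primary outcome: patients are nested within oncologists in a multilevel model, OPTION12 decides whether an intervention counts as effective, and "All analyses of effectiveness will be controlled for differences between arms at baseline as well as the two stratification variables". Those two variables are the oncologist's working status and the type of consultation. Rater is not named.

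**The concern.** Two trained raters can still differ in their average level. With one rating per instrument per consultation, such a difference enters the score directly. Rater is not a baseline characteristic of patients, so the plan to adjust for baseline differences between arms would not bring it into the model, even if one rater happened to score more of one arm.

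What is at stake is precision in the two contrasts judged on OPTION12. The source of the noise is recorded for every score, so the model could remove it at almost no cost. By contrast, the two general communication items, which are secondary, are rated by both coders in every consultation (Secondary outcomes, part A).

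**Working it through.** **Inputs from the Sample size section:** d = 0.8, ICC = 0.20, 12 oncologists per arm, 8 patients per oncologist, two-sided alpha 0.05, stated power 0.84. The training contrast uses only patients without the aid, so 4 per oncologist and 48 per arm. The aid contrast uses patients of untrained oncologists, 48 against 48.

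**Assumptions:** total planning variance 1, split into 0.2 between and 0.8 within oncologists; a 50:50 split of OPTION12 scores between raters; no random slope for the aid. D, the mean difference between raters in SD units, is not in the document and is taken over 0 to 1.0.

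**Step 1: the plan's own figure.** Design effect = 1 + (4 − 1) × 0.20 = 1.6. Effective n per arm = 48 / 1.6 = 30. SE = √(2/30) = 0.258. The noncentral t with 24 − 2 = 22 df gives power 0.8415, which matches the stated 0.84.

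**Step 2: rater variance on top of the planning SD.** With half the scores D/2 above and half D/2 below the common mean, the added variance is D²/4.

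- Training SE = √{2 × [0.2/12 + (0.8 + D²/4)/48]}, 22 df
- Aid SE = √{2 × (0.8 + D²/4)/48}, with 96 − 12 − 1 = 83 df

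| D (SD) | D²/4 | Training SE | Training power, no rater term | Aid SE | Aid power, no rater term |
|---|---|---|---|---|---|
| 0 | 0 | 0.258 | 0.842 | 0.183 | 0.991 |
| 0.25 | 0.016 | 0.259 | 0.838 | 0.184 | 0.990 |
| 0.5 | 0.063 | 0.263 | 0.828 | 0.190 | 0.987 |
| 0.8 | 0.160 | 0.271 | 0.806 | 0.200 | 0.977 |
| 1.0 | 0.250 | 0.278 | 0.786 | 0.209 | 0.966 |

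With a rater term, training power returns to about 0.84.

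**Step 3: rater variance already inside the planning SD.** Power without the term stays at 0.84. With the term, 0.8 − D²/4 replaces 0.8 + D²/4, and training power is 0.845, 0.856, 0.877 and 0.897 at D = 0.25, 0.5, 0.8 and 1.0.

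**Step 4: chance imbalance in rater mix.** The SD of the difference in rater share between two arms of 48 is √(2 × 0.25/48) = 0.102, so the contrast shifts by a typical 0.102 × D, or 0.05 SD at D = 0.5. The variance of that shift is D² × 2 × 0.25/48 = 2 × (D²/4)/48. This is exactly the term that D adds to the squared SE in Step 2, so the imbalance is that same noise seen from another side.

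**Step 5: simulation of the training contrast** (4,000 runs per setting, rater assigned at random). Type I error without a rater term was 4.9% to 5.0% for D = 0, 0.5 and 1.0; the Monte Carlo standard error is √(0.05 × 0.95/4000) = 0.3 percentage points. Power without and with the term was 0.833 and 0.848 at D = 0.5, and 0.783 and 0.835 at D = 1.0.

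**The case against.** The strongest reply is that nothing here is wrong. Assignment to raters is random, the raters are not told either condition, and the alternation spreads both instruments over the coding period. A rater covariate is the kind of detail that an analysis plan might add, and the article does not say that its covariate list is exhaustive. Up to D = 0.5 SD the training contrast loses at most 1.4 percentage points and stays above the 80% target, and the aid contrast has power to spare throughout. The effect sizes and ICCs used for planning also come from observer-rated scores, so some rater variance may already be in them. Most of this stands, and it limits the point to efficiency. What remains is that the article does state an adjustment set, that rater is not in it, and that adding rater after the data are seen would be an unplanned change to the model.

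Three stronger readings are tempting, and the document supports none of them.

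- **Bias.** A reader might infer that the effect estimates are biased. A constant rater offset assigned at random has no expected effect on either contrast. The Blinding section concedes that the aid may come up in a recording, but that is a different matter, and a rater term would not address it.
- **Two harms.** A reader might count noise and chance imbalance separately. Step 4 shows that the unadjusted standard error already covers the imbalance.
- **A very large tolerated offset.** Taken alone, the one-point limit might suggest that the raters could differ by a full point on every item. The rule also requires ICCs and average weighted kappas above .60. Under a uniform one-point offset, linearly weighted kappa cannot exceed 0.50, so the rule would fail. The article does not name the weights or the ICC type, and five recordings per instrument is a small basis, so calibration limits D without fixing its value.

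**Conclusion.** The point holds as a minor matter of efficiency. Each primary score depends on one of two raters, the stated model does not account for which, and any systematic difference between them remains as removable residual variance in both primary contrasts. There is no expected bias, and type I error holds.

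The size depends on two things that the document does not give: the rater difference D, and whether the planning SD already contains rater variance. If it does not, the loss in training power is about 1.4 points or less up to D = 0.5 SD, and power falls below 80% only somewhere between D = 0.8 and 1.0 SD. If it does, the stated 0.84 stands and the trial merely forgoes a gain. In both cases a rater term helps when the raters differ, and costs almost nothing when they do not.

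**What to change.** Add one sentence to Statistical methods, Primary outcome: the OPTION12 and 4SDM models include the rater of that score (two levels) as a fixed covariate. This should be fixed before the trial scores are analysed. It costs one degree of freedom and needs only the rater's identity stored with each score.

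Balancing the assignment of recordings to raters within oncologist and aid condition is optional. It adds little once rater is in the model, and patients excluded after randomization would disturb exact balance.
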